### Medical device

Transcranial direct current stimulation (tDCS) devices will be used in this study. This product has been CE marked, approved for depression, chronic pain and post stroke rehabilitation; it will be used as off label within the OCD population. All manufacturer guidance will be adhered to when delivering the stimulation. These will be preprogrammed to deliver either an active current or a sham stimulation. The stimulator is a modular system for direct current (DC) stimulation, designed specifically for both research and clinical use. It consists of a stimulator (HDCstim), a programmer (HDCprog) and a set of electrodes (HDCel). The basic HDCkit package contains everything required to administer tDCS. The HDCkit is fully programmable and can run any number of applications or treatments within its parameters. This device is manufactured by Newronika (Italy) and distributed by Magstim (UK).

#### HDCprog

The HDCprog is an easy-to-use touch-screen LCD programmer that, when connected to a HDCstim, allows the clinician/researcher to set tDCS treatments or protocols for their patients or subjects (e.g. active stimulation or sham, polarity, current intensity and duration). By using the HDCprog, it is possible to define an entire treatment or application by setting the number of stimulations (maximum 99), the intensity (up to 1.5 mA per channel), the duration (maximum 20 min), and the minimum interval between two consecutive simulations (max 1168 h). Upon connecting it to a HDCStim after a treatment has been administered, the HDCprog allows the physician to check stimulation results through an easy-to-navigate stimulation report interface, allowing for an informed evaluation of applications administered so far. HDCprog is powered by an AC/DC adapter, which is certified for medical use.

#### HDCstim

The HDCstim is a battery supplied, programmable stimulator that is used to administer direct current (DC) stimulation. The HDCstim is only preprogrammable with a HDCprog and will not deviate from the treatment or protocol chosen by a researcher or clinician. The HDCstim delivers a finite number of prescribed stimulations with a selectable time interval between two consecutive stimulations. The HDCstim records all use and its outputs, for later retrieval on the HDCprog by researcher or clinician. It is lightweight, highly portable and compact. Additional HDCstims can be ordered as required without the need to buy additional programmers.

#### HDCel

The HDCel is a set of accessories for the administration of DC stimulation from the HDCStim. HDCel consists of a set of electrodes made from plant cellulose and conductive silicone, and are manufactured to ensure biocompatibility with the skin. Electrodes are safely connected to HDCStim through the cables provided, the connections of which are designed to minimise the risk of incorrect set-up. Personalised sponge electrode cover, standard EEG gel and saline solution 0.9% NaCl will be applied on the HDCel to ensure optimal electrical conduction.

### Intervention

#### Preparation and labelling of the medical device

The HDCprog will be connected to the different HDCstimulators in the set-up phase of the study, and for each HDCstimulator will be defined the entire treatment application as per protocol, by setting the type of stimulation (active or sham), the intensity (2 mA) and the duration (20 min). Stimulation will take place in a quiet room. The patient sits awake in a comfortable chair. Electrodes are placed using the International 10–20 System [39]. The settings on the tDCS stimulator, marked with “1” and “2” codes known to the clinician responsible for the tDCS montage and delivery, are preselected for active or sham stimulation [40]. The clinician responsible for the montage will be instructed regarding the target site (OFC or SMA) by the external randomisation allocation. Intervention settings are unknown to the patient and the RA thus tDCS is administered in double-blind methodology. Individual sponge electrodes soaked in saline solution and standard EEG gel will be used. The active electrode is placed over the SMA (cathodal, Fz point) or left OFC (cathodal, FP1 point) and attached to the scalp using a personalised sterile head net tubular bandage. The inactive (reference electrode) is placed over the right deltoid using an elastic band. In active treatment, a 2-mA current is delivered for 20 min. Sham stimulation uses the same methodology apart from the current setting on the stimulator. Previous studies indicate that this procedure is well tolerated by participants with mental disorders, and reliability of sham procedures [24, 27, 28, 40–43].

### Stimulation schedules

The stimulation protocol in FEATSOCS has been designed according to expert recommendations regarding the safety of tDCS, developed for research ethics committees and Institutional Review Boards, as well as in clinical practice [43]. The application of tDCS has presented minimal risk in numerous research or clinical studies when applied within standard parameters. Minimal risk means there have been no serious adverse events, that common adverse effects such as reddening of the skin are mild and short-lived, and that reasonable efforts at assessment have determined there is no evidence of brain damage. Standard parameters to date mean that (1) the current is less than 2.5 mA, (2) it is applied through electrodes that are known to minimize skin burns at the specific current level, (3) the current application duration is less than 20–60 min per session, and (4) sessions are not more frequent than twice per day [42, 43]. In line with these recommendations, each participant will receive two 20-min stimulations separated by 4 h on Day 1 and on Day 2 of each session comprising:Cathodal tDCS 2 mA to the bilateral SMACathodal tDCS 2 mA to the left OFCSham tDCS to the OFC or SMA

The courses will be allocated in a randomised and counterbalanced order. Each 2-day course of tDCS will be spaced 4 weeks apart to avoid carry-over effects, and allow for the duration of effect to be evaluated. Patients will be assessed before each stimulation, up to 4 h afterward, with the assessments at 4 h after the second stimulation may be conducted over the phone, and then at 24 h and 7,14 and 28 days following tDCS stimulation.

### Measures

#### Baseline data

The following assessments will be used to gather baseline data (all outlined in Table 1).Yale-Brown Obsessive–Compulsive Scale (Y-BOCS) [44]Yale-Brown Obsessive–Compulsive Challenge Scale (Y-BOCCS Challenge): challenge version of the Y-BOCS (10), which is designed for researchers or patients to evaluate short-lived changes in symptom severity using a visual analogue scale [45]Clinical Global Impressions Scale (CGI-S) [46]Montgomery-Åsberg Depression Rating Scale (MÅDRS) [47]Barratt Impulsiveness Scale (BIS) [48]Sheehan Disability Scale (SDS) [49]Neurocognitive tests: CANTAB (Stop Signal Reaction Time Test, Intra-Extradimensional Set Shift), Prisoner’s Dilemma test (cooperation test). The Fabulous Fruit game (habit learning test): only patients who have attended a screening appointment in person prior to the 13th March 2020 (when research activity was paused due to COVID-19) will be assessed using the Fabulous Fruits Game on stimulation days. Patients who are screened over the phone, will not be familiarised with the Fabulous Fruits Game (as it is not possible to do this remotely) and therefore will not be assessed using the Fabulous Fruits Game on stimulation days.

**Table 1 Tab1:** Table of study assessments

Conducted By	Test	Screening (completed by Clinician)	In centre assessments for each of 3 sessions (Sham, OFC, SMA) Day 1										In centre assessments for each of 3 sessions (Sham, OFC, SMA) Day 2									Follow-up via telephone^b^		
			Baseline	Intervention	1 h	2 h	3 h	4 h	Intervention	1 h	2 h	4 h	0 h	Intervention	1 h	2 h	4 h	Intervention	1 h	2 h	4 h	24 h	7 days	14 days
DR	DSM-5	X																						
DR/RA	Y-BOCS	X	X										X									X	X	X
DR/RA	Y-BOCS Challenge		X		X	X		X		X	X	X	X		X	X	X		X	X	X	X	X	X
RA	CGIS		X										X									X	X	X
DR/RA	MÅDRS	X	X																			X	X	X
RA	BIS		X																					
RA	SDS		X																			X	X	X
RA	CANTAB		X				X																	
RA ^a^	AEs		X		X	X		X		X	X	X			X	X	X		X	X	X	X	X	X
DR	Clinical Review		X					X			X		X				X			X				
	**Time (min)**	**60**	**105**	**20**	**15**	**15**	**30**	**30**	**20**	**15**	**15**	**30**	**30**	**20**	**15**	**15**	**20**	**20**	**15**	**15**	**30**	**15**	**15**	**15**

^a^The RA will complete the AE questionnaire with participants and refer to the clinician if necessary

^b^There will be an additional telephone call at 28 days only after the patients have completed the last arm of the intervention. The assessments will be the same as the previous phone calls (prior to this, day 28 will be day 1 of the next intervention arm that the patient completes)

Adverse events will be recorded using a questionnaire developed by Brunoni et al. [50] developed specially for tDCS. This asks patients to rate 10 symptoms on a scale of 1–4 (see Table 2).

**Table 2 Tab2:** tDCS Adverse Effects Questionnaire

tDCS Adverse Effects Questionnaire – Session ____________________			
Do you experience any of the following symptoms or side effects?	Enter a value (1–4) in the space below (1, absent; 2, mild; 3, moderate; 4, severe)	If present: Is this related to tDCS? (1, none; 2, remote; 3, possible; 4, probable; 5, definite)	Notes
Headache Neck pain Scalp pain Tingling Itching Burning sensation Skin redness Sleepiness Trouble concentrating Acute mood change Others (specify)			

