#### Long-term follow-up assessments

Patients will be followed up 7, 14 (via telephone) and 28 days (in clinic at their next stimulation cycle and in clinic or via telephone at the last study follow-up planned 28 days after the final stimulation) after their participation in the study, using the Y-BOCS, Y-BOCCS challenge, MÅDRS, SDS and the CGIS by the RA. Any reported adverse events will be followed up by the clinician by phone; if deemed necessary, the patient may be asked to come back to the clinic.

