#### First visit (Day 1)

•Patients will be consented then randomised by a clinician who will later deliver the intervention. As patients will be unable to drive after receiving the stimulation, the clinician will check that suitable transport arrangements are in place.

•Pregnancy test the first day (if applicable); pregnancy and reliable contraception questionnaire at each visit

•The RA will then complete baseline assessments with the patient, as in the table of study assessments (see Table 1).

•The patient will then be taken to a room where the intervention will be delivered by the clinician. Blood pressure and heart rate will be measured by the clinician before and after the stimulation.

•After the 20-min intervention is complete, the patient will be given somewhere to wait, and will be followed up by the RA on a regular basis using the Y-BOCS challenge as well as noting any adverse side effects. A questionnaire developed by Brunoni et al. (2011) designed to record adverse events (AEs) related to tDCS will be used.

•Neurocognitive tests at 3 h

•Four hours after the intervention, the clinician will return to review the patient then deliver the intervention a second time, again for a duration of 20 min.

•The patient will be asked to wait again in the centre, and followed up by the RA for the duration of 2 h using the Y-BOCS challenge, as well as noting any adverse events (AEs).

•The clinician will review the patient before they leave, inclusive of checking the patient’s blood pressure and heart rate.

•The RA will phone the patient to conduct the assessments at 4 h after the second stimulation.

•It is anticipated that the patient will be in the centre for 8 h on the first visit.

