#### Follow-up via telephone

•The RA will follow up with patient via telephone, 24hours, 7 days and 14 days after the second visit. The last study follow up will be 28 days after the final stimulation.

After a 4 week wash-out period, this 2 day cycle will be repeated using a different intervention according to which of the 6 permutations the patient is randomised to receive. Patients will be required to keep their current psychiatric medication dose stable and not to initiate cognitive behaviour therapy during the 12 weeks of the study. This is to avoid any effect of change in treatment being recognised as a change resulting from the treatment provided in the study. Should these restrictions prove unacceptable or a change in treatment is required for a clinical reason the patient will be withdrawn from the study.

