##### Duration of effect

Change over time will be evaluated separately for the OFC and SMA targets using paired tests, identifying the time point (1, 2 and 4 h or 1, 7 and 14 days) at which the Y-BOCS returns to pre-stimulation levels. A mixed model may be evaluated where this may provide additional useful information about the trajectory of the Y-BOCS score over time (growth models).

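### The duration-of-effect analysis compares telephone ratings on a visual analogue scale with an in-centre baseline, within each target and without Sham, so a clinic-to-telephone shift would be read as a lasting or a lost effect

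*Protocol article*

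**What the plan says.** All references are to the protocol article.

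- **Instrument.** Baseline data introduces the Y-BOCS Challenge as a version of the Y-BOCS "which is designed for researchers or patients to evaluate short-lived changes in symptom severity using a visual analogue scale". Table 1 lists it as conducted by the doctor or the RA. Sample size calculation names the difference in this scale between tDCS and Sham as the primary outcome.
- **Mode before and shortly after stimulation.** Table 1 places baseline and all Day 1 and Day 2 readings under headings such as "In centre assessments for each of 3 sessions (Sham, OFC, SMA) Day 1".
- **Mode at 24 h and later.** Follow-up via telephone states: "The RA will follow up with patient via telephone, 24hours, 7 days and 14 days after the second visit".
- **Mode at 4 h after each day's second stimulation.** Table 1 has this in the centre. Stimulation schedules leaves it open ("with the assessments at 4 h after the second stimulation may be conducted over the phone"). The Day 1 and Day 2 visit sections make it a call: "The RA will phone the patient to conduct the assessments at 4 h after the second stimulation".
- **Mode at 28 days.** Long-term follow-up assessments has it "in clinic at their next stimulation cycle and in clinic or via telephone at the last study follow-up planned 28 days after the final stimulation". Footnote b to Table 1 describes the reading after the last arm as a telephone call.
- **Analysis.** Likely effect size takes the main comparison at 24 h after the final stimulation, each target against Sham. Duration of effect works separately within OFC and within SMA by paired tests, "identifying the time point (1, 2 and 4 h or 1, 7 and 14 days) at which the Y-BOCS returns to pre-stimulation levels". It does not mention Sham.

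**The concern.** A visual analogue scale depends on how it is presented. Rated in person with the line on the table, or by voice over a telephone, the same symptom state may yield a different number. In this plan every reading at 1, 7 and 14 days is by telephone and every pre-stimulation reading is in the centre. Within one target, a change of mode and a change over time cannot be told apart.

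A telephone shift towards lower scores would look like an effect that persists. A shift towards higher scores would look like a return to baseline. Duration of effect is a listed secondary objective, intended to guide how treatments are spaced, so a wrongly dated loss of effect would carry into the schedule of the definitive trial.

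**Working it through.** **1. Reproduce the plan's own figure.** Sample size calculation gives power for paired t tests with N = 20: 0.78 at d = 0.65 and 0.90 at d = 0.77, with α = 0.05 (sidedness not stated).

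Formula: with 19 degrees of freedom, critical value c = t(0.975; 19) = 2.093 and noncentrality δ = d√20, power = P(|T| > c), where T is noncentral t with parameter δ.

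- d = 0.65: δ = 2.907, power 0.787
- d = 0.77: δ = 3.444, power 0.904

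Both agree with the stated values. A one-sided test (0.876 and 0.953) and a two-sided normal approximation (0.828 and 0.931) do not, so the two-sided paired t test is used below.

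**2. Where a mode shift goes.** Let e be the true remaining effect of a target relative to Sham, and m a constant shift added to every telephone score. Both are in SDs of the paired differences, positive in the direction of improvement. For simplicity, let Sham have no change of its own.

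- Change from in-centre baseline to a telephone reading, within a target: e + m
- The same change within Sham: m
- Target minus Sham at the same time point: (e + m) − m = e

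The within-target change carries the whole of m. The contrast with Sham carries none of it, because all three conditions follow the same assessment schedule.

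**3. Illustration for the within-target test.** The size and sign of m are assumptions; the documents give neither. Step 1's formula is applied with d replaced by |e + m|.

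| True remaining effect e | Shift m | Observed e + m | P(significant difference from baseline) |
|---|---|---|---|
| 0 | 0 | 0 | 5.0% |
| 0 | ±0.1 | ±0.1 | 7.1% |
| 0 | ±0.2 | ±0.2 | 13.6% |
| 0 | ±0.3 | ±0.3 | 24.7% |
| 0.65 | 0 | 0.65 | 78.7% |
| 0.65 | −0.1 | 0.55 | 64.6% |
| 0.65 | −0.2 | 0.45 | 48.0% |
| 0.65 | −0.3 | 0.35 | 31.8% |
| 0.65 | +0.3 | 0.95 | 98.1% |

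**4. Which scale and which time points.** Duration of effect says Y-BOCS. At 1, 2 and 4 h Table 1 schedules only the Challenge version, so that scale must be meant there. At 1, 7 and 14 days Table 1 has both scales, both by telephone, so the change of mode applies whichever is used; the visual-scale argument applies to the Challenge only. If the visit sections are followed, the mode already changes between 2 h and 4 h after each day's second stimulation. The 28-day reading is not among the time points listed in Duration of effect.

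**The case against.** The strongest case against has four parts.

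**The mechanism is not shown.** Table 1 has the doctor or RA conduct the Challenge, and the mention of researchers or patients describes what the scale was designed for, not who completes it here. How a scale is given over the telephone is a detail an article may leave to the full protocol. This stands in part. A reader might infer that patients mark the line themselves in the centre and cannot do so by telephone; the article does not establish that. But the change of mode, and the within-target comparison across it, are fixed in the article itself, and rating in person and rating by voice are different modes even with the same RA.

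**The main comparison is untouched.** This stands. A reader might infer that the 24 h effect size against Sham, and hence the progression decision, is biased. It is not: a shift common to all conditions cancels (step 2). Bias there would need a shift that differs by condition, which nothing in the article suggests. One might also argue that telephone scores are noisier and widen the interval, but the article gives nothing from which to judge or size that.

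**The magnitude is assumed.** This stands; the figures show sensitivity, not an expected bias.

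**The plan already holds a partial remedy.** Effect of tDCS estimates scores at all time points in all three conditions, so a common shift would be visible in the Sham course, and Duration of effect allows a mixed model. True, but the stated rule for dating the return to baseline does not use Sham.

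At 28 days, only the reading after the last course can be by telephone. The six permutations put each condition last equally often, so no condition is systematically favoured.

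**Conclusion.** The point holds for the duration-of-effect analysis and for any other within-target change from the in-centre baseline to a telephone reading. There, mode is fully confounded with time, and the paired tests as written cannot separate the two. With 20 completers, a two-sided 5% paired t test and an assumed constant shift of 0.2 to 0.3 SD of the paired differences, the false finding of a remaining effect rises from 5% to 14–25%. A shift of the same size in the other direction cuts power at d = 0.65 from 79% to 48–32%. The true shift may be smaller, larger or nil.

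The point does not extend to the 24 h contrast with Sham. Separately, and whatever the size of a mode effect, the article disagrees with itself on mode at 4 h after each day's second stimulation and at 28 days after the last course. The change is worth making because it is cheap and the confounding cannot be undone within a target afterwards.

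**What to change.** 1. Keep the blinded RA as rater of the Y-BOCS Challenge. Use the same script and the same printed scale sheet in the centre and by telephone, giving the patient a copy on Day 1 to have at hand during calls.
2. Add one case report form field for the mode of each reading (clinic or telephone).
3. In Duration of effect, date the loss of effect by the target-minus-Sham difference at each time point, where a common shift cancels. State which scale, Challenge or full Y-BOCS, is meant at each time point.
4. Reconcile the mode at 4 h after the second daily stimulation (Table 1, Stimulation schedules, and the Day 1 and Day 2 visit sections) and at 28 days after the last course (footnote b to Table 1 and Long-term follow-up assessments).

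Patient-marked sheets returned by post are not advised: they would replace a fully blinded rater with a patient whom the Blinding section calls only partially blinded. A mode term in the model for day 28 would not help much either, since telephone readings there can occur only after the third course and so are confounded, or nearly so, with period.

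Cost: a printed sheet, a short script, one form field and a few sentences of text. There may also be some loss of precision. If change has the same SD in both conditions and correlation r between them, the SD of target minus Sham is √(2(1 − r)) times the SD of a within-target change: 1.41 times at r = 0, and no larger at r = 0.5. The correlation is not given. At r = 0, a within-target effect of 0.65 corresponds to 0.65/1.41 = 0.46 on the new scale, with power of about 50% at n = 20. It is therefore better to report the difference with its interval at each time point than to rely on a significance test to date the return.

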#### Acceptability, tolerability and safety

Treatment logs will be maintained, and the number of completed, shortened and missed sessions will be summarised by treatment condition. Reasons for refusal to complete or missing a treatment session will be recorded and tabulated. Comparison between treatment conditions will be evaluated using a McNemar test.Incidents related to safety and tolerability will be logged during the exposure to tDCS and in the following weeks. The nature of the adverse events will be documented, classified (as outlined in the “Measures” section) and listed. The number of scope of the events in each of the study conditions will be compared using a McNemar test.

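### The adverse-event form states no reference period, yet it is reused at follow-up contacts 6, 7 and 14 days apart, so short-lived late events may be under-recorded.

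*Protocol article*

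**What the plan says.** The Measures section (Baseline data) names the tool: "Adverse events will be recorded using a questionnaire developed by" a cited author group, designed for tDCS. Table 2 prints it. The title line has a blank for the session, and the question reads "Do you experience any of the following symptoms or side effects". Ten symptoms and an open Others line are graded from absent to severe. Relatedness is asked only where a symptom is present, and there is a Notes column. No column holds a time window, an onset or an end.

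Table 1 ticks the adverse-event row at baseline, at 1, 2 and 4 hours after each of the four stimulations, and at the 24-hour, 7-day and 14-day calls. Footnote a says who fills it in: "The RA will complete the AE questionnaire with participants and refer to the clinician if necessary". The follow-up section sets the calls: "The RA will follow up with patient via telephone, 24hours, 7 days and 14 days after the second visit". Footnote b adds day 28: "There will be an additional telephone call at 28 days only after the patients have completed the last arm of the intervention". For the earlier arms it states that "prior to this, day 28 will be day 1 of the next intervention arm that the patient completes".

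The analysis section on acceptability, tolerability and safety sets the aim: "Incidents related to safety and tolerability will be logged during the exposure to tDCS and in the following weeks". Events are to be classified as the Measures section describes and compared between conditions.

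**The concern.** A present-tense rating suits the hours after a stimulation. At a call one or two weeks after the last contact, it leaves open whether the patient should report only what is felt now or everything since that contact. A headache that came and went on days 3 to 4 can properly be scored absent on one understanding and present on the other. Two things may follow: late transient events are under-counted, and answers are not comparable between patients or between the two sites.

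Safety and tolerability are among the stated feasibility objectives. The sample size section says that the number of adverse events cannot be estimated in advance, so this study has to supply the rate on which the full trial will be planned. An under-count of late events would carry over into that planning.

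There is also an attribution problem. In the first two arms the day-28 contact is the baseline of the next arm. Without an onset date, a symptom noted there cannot be placed firmly in the preceding condition, although the counts are compared by condition.

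**Working it through.** **Inputs from the protocol article**
- Follow-up contacts at days 1, 7, 14 and 28 (Table 1, footnote b, Follow-up via telephone).
- Adverse-event readings per course (Table 1): 1 baseline + 4 stimulations × 3 readings + 3 calls = 16. Of these, 12 fall 1 to 4 hours after a stimulation.
- Clinical review row (Table 1): no tick at the 24-hour, 7-day or 14-day call. At those calls the research assistant's form is the only scheduled adverse-event question.
- No adverse-event rate or symptom duration is given, so there is no figure of the plan's own to reproduce.

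**Gaps:** 7 − 1 = 6 days, 14 − 7 = 7 days, 28 − 14 = 14 days; 27 days in all.

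**Illustration under a strict present-now reading.** Assume that onset is uniform over a gap of G days, that the event lasts D days, and that nothing is volunteered. The event is still present at the next contact with probability min(D, G)/G. Over days 1 to 28 the share caught is the sum of min(D, G) over the three gaps, divided by 27. The durations are assumptions.

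| D (days) | G = 6 | G = 7 | G = 14 | Days 1 to 28 |
|---|---|---|---|---|
| 1 | 1/6 = 17% | 1/7 = 14% | 1/14 = 7% | 3/27 = 11% |
| 2 | 2/6 = 33% | 2/7 = 29% | 2/14 = 14% | 6/27 = 22% |
| 3 | 3/6 = 50% | 3/7 = 43% | 3/14 = 21% | 9/27 = 33% |
| 7 | 100% | 100% | 7/14 = 50% | 20/27 = 74% |

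**Effect on a count.** If 5 of 25 patients (20%, assumed) had a 1-day headache between the 24-hour and 7-day calls, 5 × 1/6 = 0.8 would be recorded, or 20% × 1/6 = 3.3%.

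**Effect on a comparison.** Take assumed true risks of 20% on active and 5% on sham. The recorded risks become 20/6 = 3.3% and 5/6 = 0.8%. The absolute difference falls from 15 to 2.5 percentage points. The ratio stays at 4.

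**With a since-last-contact question,** all 27 days are covered, apart from forgetting.

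**The case against.** A reader might infer that the form asks only about the moment of contact, that events between calls are therefore not recorded, and that safety will look better than it is. The documents do not support this:

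- The question does not say now or today. A patient asked on day 7 may well mention a headache from day 3.
- There are other routes. The form has Others and Notes. The Long-term follow-up section has the clinician pursue any reported event. The End of trial section has the research psychiatrist assess tolerability. The analysis section commits to logging over the following weeks. Mood at follow-up is also covered by the MÅDRS at each call.
- The acute period is sampled densely, and the Stimulation schedules section describes common effects as mild and brief.
- Form and schedule are the same for sham, OFC and SMA, so neither favours a condition.
- The article condenses a fuller protocol, and recall instructions or date fields may sit in the electronic case report form.

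Most of this stands and limits the claim to a possible under-count. It does not remove the point. The other routes deal with events once reported, or with general tolerability; none is described as asking about symptoms that have resolved. Others and Notes let a patient volunteer a past event but do not prompt for one. The logging commitment leads back to the Measures section for classification and adds no other question. The form is printed in the article, so its poor fit to the follow-up calls is visible in the text and is not merely a detail left out. If a recall instruction exists elsewhere, the sponsor need only confirm it and print it on the form.

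**Conclusion.** The point holds as a weakness of the printed instrument at follow-up. A per-session, present-tense form without a reference period or onset date is reused across gaps of 6, 7 and 14 days. Late transient events may go unrecorded and patients may answer for different windows. Late counts may therefore be too low in every condition, and an absolute active-sham difference in late events may shrink, while a ratio would be broadly preserved.

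The size cannot be known from the documents. The 17%, 14% and 7% capture figures for a 1-day event rest on an assumed duration, uniform onset, a strict present-now reading and no volunteered reports. They are not an estimate for this trial. The concern does not extend to the hours after stimulation. It is worth correcting because safety is a stated objective and the change is cheap.

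**What to change.** From the 24-hour call onward, including the day-28 contact, ask each Table 2 symptom and the Others item as 'since our last contact', with worst severity and onset and end dates. At day 28 in the first two arms, ask this before the new course starts, so that events can be assigned to the preceding condition. Keep the present-tense rating at 1, 2 and 4 hours. Base the follow-up part of the per-condition event counts on the since-last-contact answers.

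The cost is a follow-up version of the form and a few minutes per call. The downsides are a small departure from the published wording and reliance on one to two weeks' recall. Because the Trial status section says that recruitment is under way, the form version used at each contact should be recorded, so that counts taken under the two wordings can be told apart.
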